### Implementation process of the intervention

The intervention clinics received the EMPOWER-PAR intervention package, which consists of CDM workshops, intervention tools, facilitation and support for a period of one year.

The implementation process was conducted in 3 phases: Phase 1: Formation and training of the CDM teamPhase 2: Distribution of the intervention tools

Global CV Risks Self-Management BookletsCPG to assist with clinical decision making

Phase 3: Facilitation and support to implement the intervention

#### Phase 1: Formation and training of the CDM team

Each intervention clinic was required to identify at least five CDM team members, including the FMS, medical officer, medical assistant, nurse, pharmacist and dietician/nutritionist. The team was required to be led by the FMS and was trained in the CDM Workshops.

The CDM workshops consisted of three workshop series of 1.5 days each, and the objectives and contents were designed based on the six interrelated elements of the CCM. These workshop series were piloted in an urban public primary care clinic in Negri Sembilan. Written and verbal feedback regarding the workshop was obtained from the participants. The workshop’s objectives, content and teaching and learning methods were then refined accordingly. Table 2 summarises the finalised CDM workshop’s objectives, content and teaching and learning methods. During the workshop, the CDM team from each clinic was divided into small groups to discuss the challenges and brainstorm on the details of how best to deliver the intervention within their limitations and constraints. At the end of the workshop series, the CDM team from each clinic prepared a proposed intervention plan describing the steps needed to achieve their goals within a set timeline. The agreed plan of action took into account their constraints and how to overcome those barriers.

**Table 2 Tab2:** **EMPOWER-PAR CDM Workshops’ Objectives, Contents and Teaching–Learning Methods**

Workshops	CCM elements covered	Objectives	Contents	Teaching-learning methods
Workshop 1	• Organisation of health care (providing leadership and removing barriers to care)	At the end of this workshop, the participants should be able to:	1. Introduction to CDM and CCM	• Lecture
	• Delivery system design (coordinating care processes)	• Discuss the concept and principles of CDM & the CCM	2. Redesigning delivery of care for chronic conditions	• Small group hands-on sessions
		• Discuss the need to coordinate care for chronic conditions using multidisciplinary care team	3. Building a multidisciplinary CDM Team	• Group presentation
		• Define roles and responsibilities of the team members	• Defining roles and responsibilities	
		• Formulate a plan on how to re-design the delivery of chronic care in your own practice setting	• Identifying barriers and resolving potential conflicts	
		• Formulate a plan on how to improve care coordination	• Improving care coordination	
			4. Delivery system re-design to improve care coordination	
			• Developing clinic-based registries	
			• Creating appointment system, reminder mechanisms and defaulter tracing	
Workshop 2	• Self-management support (facilitating of skills-based learning and patient empowerment)	At the end of this workshop, the participants should be able to:	1. Introduction to self management support	• Lectures
		• Discuss the concept and principles of self-management support	2. Patient-centred communication:	• Small group hands-on sessions
		• Demonstrate patient-centred consultation to support patients’ self-management	• Building relationship and partnership	• Consultation practice of various clinical scenarios using simulated patients and the Global CV Risks Self-Management Booklet as a tool
		• Guide patients to make informed decision	• Shared decision making	
		• Motivate patients to change their behaviour	3. Building Relationship	
		• Utilise the Global CV Risks Self-Management Booklet to empower patients	• Gathering clinical information & patient experience	
			• Exploring ideas, concerns and expectations	
			• Engaging patient	
			4. Sharing information and goal setting	
			• Providing sufficient information	
			• Explaining in simple language	
			• Assessing understanding	
			• Goal setting	
			5. Reaching agreement in management plan	
			• Involving patient in decision making process	
			• Reaching agreement	
			6. Motivating patients to change	
			• Motivating patients to change their lifestyle	
			• Achieving adherence to therapy	
			• Self-monitoring of blood pressure and blood glucose	
			• Supporting patients with self management tools	
Workshop 3	• Decision support (providing guidance for implementing evidence-based care)	At the end of this workshop, the participants should be able to:	1. Introduction to evidence-based care and decision support	• Lectures
	• Clinical information systems (tracking progress through reporting outcomes to patients and providers)	• Discuss the importance of evidence-based care	2. Implementing CPG	• Small group hands-on sessions
	• Community resources and policies (sustaining care by using community-based resources)	• Identify potential solutions to improve CPG implementation in primary care clinics	• Identifying facilitators for change and possible solutions	
		• Utilize the T2DM and HPT CPG to aid management and prescribing.	• Using CPG in daily clinical practice	
		• Formulate a plan on how to improve the clinical information system (CIS)	3. Improving CIS and designing a clinical audit project	
		• Discuss the importance of Clinical Audit in improving quality of chronic disease management	• Identifying areas needing improvement	
			• Sampling frame and sample sizes	
			• Sampling methods	
			• Activity charts	
		• Design a Clinical Audit Project	• Criteria and standards	
		• Recommend remedial actions to improve chronic care quality	• Preparing data collection format	
			• Data analysis and interpretation of results	
			• Remedial action plan and	
		• Discuss the importance of community resources	• Implementation	• Group presentation
			• Completion of the audit cycle	
			• Distributing tasks among team members	
			4. Community Resources	
			• Identifying available resources in your community	
			• Developing collaborative partnership with NGO’s and community leaders	

Apart from the CDM workshop, an intervention review workshop was conducted 6 months after the commencement of intervention. In this workshop, the intervention clinics were invited for a 1-day session to share their experiences and challenges in implementing the intervention. The main objective of this workshop was to allow interactions among the participating clinics and solve any arising problems.

#### Phase 2: Distribution of the intervention tools

The intervention tools consist of the i) Malaysian CPG and the Quick References (QR) on the Management of T2DM [42] and HPT [43] to assist health care providers in clinical decision making; and ii) the Global CV Risks Self-Management Booklet to support patients’ empowerment and self-management skills in managing their T2DM and/or HPT.

The CPG and QR were distributed to the CDM team during the third CDM workshop, where they were trained on how to recognise the facilitators and barriers for CPG utilisation and on how to find solutions to improve CPG utilisation in their daily clinical practice. CPG training using interactive case discussion was also conducted during the intervention review workshop.

The Global CV Risks Self-Management Booklet was designed by the investigators to suit local needs. It was a 49-page booklet that is divided into four sections. The first section contained information to empower patients with knowledge regarding their global CV risks (including T2DM, HPT, dyslipidaemia, overweight/obesity, cigarette smoking and family history of premature CVD), presence/absence of complications, CV risk stratification and treatment targets. The second section contained on-going information of the patient’s routine physical examination findings and investigation results. The third section contained instructions on how to perform self-monitoring of blood glucose and home BP monitoring and dedicated pages where patients could record their own readings. The fourth section contained the patient’s medications record. Health care providers were trained on how to use the booklet to support patients in self-management of T2DM and/or HPT during the second CDM workshop. The information and instructions were written in English and Malay. At least 5000 booklets were distributed to each intervention clinic, and this booklet was given to all T2DM and/or HPT patients registered in the clinic.

#### Phase 3: Facilitation and support to implement the intervention

Each clinic was assigned two facilitators to coach the CDM team, facilitate and guide the implementation of intervention and provide feedback on their performance. Facilitators were the investigators, all of whom are qualified FMS or clinical epidemiologists. The facilitators conducted two follow-up site visits over the 1-year intervention period. The visits occur at 3 months and 9 months. During the visits, the facilitators met the CDM team to collect information on the implementation process, discuss the challenges and document the progress in the clinics. Similar data were also collected during the intervention review workshop at 6 months. This information was analysed, and detailed feedback were then provided to each clinic. It is believed that, through this collaborative process of coaching and feedback sessions, optimal implementations tailored to the needs of each clinic could be achieved.

The control clinics continued with usual care with no additional intervention. The CDM workshop modules and intervention tools will be made available to the control clinics at the end of the study. There were no other additional resources allocated to either the intervention or the control group.

### Outcome measures

Outcome measures were obtained from both intervention and control clinics at baseline and one year after the commencement of the intervention.

#### Primary outcomes

For T2DM patients, the primary outcome is measured by the change in the proportion of patients achieving the glycaemic target of HbA1c < 6.5%.

For HPT patients without T2DM, primary outcome is measured by the change in the proportion of patients achieving the BP target of < 140/90 mmHg.

#### Secondary outcomes

The secondary outcomes were measured by changes in the proportions of patients achieving the following targets:

BP ≤ 130/80 mmHg (for T2DM patients)BMI < 23 kg/m^2^Waist Circumference (WC) < 90 cm for men, < 80 cm for womenTotal cholesterol (TC) ≤ 4.5 mmol/LTriglycerides (TG) ≤ 1.7 mmol/LLDL-C ≤ 2.6 mmol/LHigh density lipoprotein cholesterol (HDL-C) ≥ 1.1 mmol/L

Other secondary outcome measures include:

Change in the process of care related to the management of T2DM and HPTChange in the medication adherence level as measured by the 8-item Morisky Medication Adherence Scale (MMAS-8) [62]Change in the prescribing patterns of antihypertensive agents, oral hypoglycaemic agents, insulin usage and lipid lowering agentsPatients’ perceptions and experiences of receiving care for chronic conditions as measured by the Patients Assessment of Chronic Illness Care (PACIC) score [63]Health care providers’ perceptions, attitudes, experiences and perceived barriers in implementing the EMPOWER-PAR intervention as measured by qualitative analysisCost-effectiveness of the EMPOWER-PAR intervention

### Study procedures

All interviewers and investigators were trained regarding the study procedures prior to the conduct of the study to minimise variability in the method of data collection. At baseline, an interview and physical examinations were conducted. Fasting venous blood samples were obtained.

#### Demographic and anthropometric data collection

A standardised case report form (CRF) was used to collect socio-demographic information on the study subjects (age, gender, ethnicity, patient contact details, education attainment and occupation), smoking status (including the number of cigarettes smoked per day for current smokers) and other clinical information (presence of comorbidities, past medical history and family history). Data on pharmacological treatment were systematically collected from the medical records of the study subjects using CRF at baseline and at 1-year follow-up in both the intervention and the control clinics. Prescribing patterns will be analysed to assess adherence to the evidence-based prescribing recommended by the CPG.

Height and weight were measured using the Seca 769 Digital Medical Scale stadiometer. Weight was measured in light clothing, without shoes on the scale with a precision of 0.1 kg. Height was measured to 0.1 cm using the stretch stature method of the stadiometer and then converted to metres. BMI was calculated using the standard formula (weight in kg)/ (height in metres)^2^. WC was measured to the nearest 0.1 cm using non-stretchable measuring tape with the subjects standing in a relaxed position and arms at the side. The measurement was taken at the midpoint between the lower rib margin (12^th^ rib) and the iliac crest.

BP was measured twice, two minutes apart on the right arm in sitting position, using an Omron IA2 model automatic digital blood pressure monitor. Subjects were made to rest for at least 5 minutes before the measurements were taken. Each subject was seated upright with his/her right arm supported at the heart level. The mean of the first and second systolic and diastolic measurements was reported as the BP value for individual subjects.

#### Blood sampling and biochemistry profile

The baseline and outcome blood samples were analysed at the Centre for Pathology and Diagnostic Research Laboratory (CPDRL), Universiti Teknologi MARA (UiTM). Overnight fasting venous blood samples were collected following non-traumatic venepuncture. Serum separated within two hours of collection was analysed for TC, TG and HDL-C using enzymatic colourimetric reference methods on an automated analyser (Roche COBAS Integra® 400, USA). Coefficient variations (CVs) for TC, TG and HDL-C were 1.2, 3.1 and 1.0 percent, respectively, which fulfilled the Westgard and Royal College of Pathologists of Australasia CVs level. LDL-C concentration was derived by calculation using the Friedewald equation [64]. HbA1c determination was based on the turbidimetric inhibition immunoassay analysed on a similar automated analyser as that of the lipid profile with CV of 0.5, which fulfils the National Glycohaemoglobin Standardisation Program. This method has been standardised against the approved International Federation of Clinical Chemistry reference method.

### Study tools

#### Process of care questionnaire

The ‘Process of Care Questionnaire’ was used to measure the indicators of care in T2DM and HPT management. This questionnaire was developed by the investigators, and it consists of four main sections outlining 12 indicators, each with a dichotomous response (yes/no). The indicators were set based on the Malaysian CPG on the Management of T2DM [42] and HPT [43]. Data were collected from the patients’ medical records in both the intervention and the control clinics, retrospectively for two points in time (i.e. at baseline and at 1-year follow-up).

#### 8-Item Morisky Medication Adherence Scale

A previously validated Malay version of MMAS-8 [62] was used for the assessment of medication adherence levels. MMAS-8 consists of eight items with a dichotomous response (yes/no) for items 1–7 and a five-point Likert response for the last item. The total score ranges from 1 to 8, with a higher total score indicating higher medication adherence level. Scores of 1–5 indicate low adherence, 6–7 indicate moderate adherence and a score of 8 indicates high adherence level. Data collection was done by face-to-face interviews of the study patients by trained researchers. Data were collected at two points in time (i.e. at baseline and at 1-year follow-up).

#### Patients Assessment of Chronic Illness Care (PACIC) questionnaire

The quantitative measurement of patients’ perceptions and experiences of receiving care for chronic conditions was made using the PACIC questionnaire [63], which was translated into Malay language, cross-culturally adapted and validated by the investigators prior to the commencement of the study. PACIC is a 20-item patient self-report instrument to assess the extent to which patients with chronic disease receive care that aligns with the CCM, measuring care that is patient-centred, proactive and planned and which includes collaborative goal setting, problem-solving and follow-up support [63].

### Qualitative data collection procedure

A phenomenological qualitative approach using focus group discussions [65] was taken to explore health care providers’ perceptions, attitudes and perceived barriers in implementing the EMPOWER-PAR intervention at their facilities. Purposive sampling was employed, whereby the CDM team members involved in the study were invited to participate. They were then divided into three groups consisting of an FMS group, a medical officers group and an allied health care personnel group. The allied health care personnel group consisted of staff nurses, assistant medical officers, pharmacists and dieticians. A total of six groups were interviewed using a semi-structured focus group topic guide focussing on their perceptions, attitudes and perceived barriers towards implementing the EMPOWER-PAR intervention at their facilities. The discussions were audio-recorded and transcribed verbatim, systematically arranged and managed by NVivo version 10 software. Thematic analysis is used to analyse the interview transcripts. Two researchers analyse the data independently.

### Cost-effectiveness analysis

Cost-effectiveness analysis was performed from the health care providers’ perspective. The cost and outcome of the intervention program was discounted at 3% as the study time horizon is two years [66]. Resources consumed in the health care sector would include patient treatment and the EMPOWER-PAR intervention cost. Data on patient treatment cost were collected using a standardised data collection form and were valued using a bottom-up approach whereby the frequency of utilisation for each patient was multiplied by the specific charge/price. As the intervention was expected to change the consultation practice in primary care clinics, the unit cost for outpatient visits was estimated using a micro-costing approach, whereby the duration of time that a patient spent on each identified activity in an outpatient visit was measured using the time-motion technique and valued based on the local centre price. The cost of the intervention (including the CDM training workshop, a module for the trainer, Global CV Risks Self-Management Booklet for the patient and continuous support from the facilitators) was estimated using a mix of top-down and bottom-up approaches. The average total cost per patient of the intervention and control group was arithmetically expressed as follows:

The cost was expressed in 2012 Malaysian Ringgit (MYR) (USD 1 = MYR 3.30). If the intervention group was statistically more expensive and effective than usual care group, then the incremental cost effectiveness ratio was calculated as the difference between the costs for each group divided by the difference in effectiveness. The threshold of MYR 31,195 was used to determine the cost-effectiveness of the intervention [67].

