**Discussion:**

Results from this study will provide objective evidence of the effectiveness and cost-effectiveness of a multifaceted intervention based on the chronic care model in resource-constrained public primary care settings. The evidence should instigate crucial primary care system change in Malaysia.

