#### Sample calculation for T2DM patients

A sample size of 626 (313 in each arm) was obtained by sampling 10 clusters (5 intervention vs 5 control) with 63 subjects from each cluster to achieve 91% power to detect 25% difference in the proportion of subjects achieving target HbA1c < 6.5% from baseline and between the intervention and control groups. The test statistic used was the two-sided Z-test (unpooled). The significance level of the test is 0.05. Therefore, after allowing for 25% dropout rate, this study aimed to recruit a total sample of 836 T2DM patients at baseline (i.e. 418 in each arm and 84 from each clinic).

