## Discussion

The EMPOWER-PAR is the first pragmatic randomised controlled trial of multifaceted chronic disease management strategies conducted in the Malaysian public primary care setting. It is expected to yield important new evidence on the improvements of T2DM and HPT clinical outcomes, the two most prevalent chronic diseases being managed in the public primary care sector. The EMPOWER-PAR hypothesised that patients’ clinical outcomes, namely HbA1c, BP, fasting serum lipid, BMI, WC, medication adherence and their perception and experience of receiving chronic disease care would improve with the EMPOWER-PAR intervention. It also hypothesised that improvements would occur at the primary care provider level in terms of the process of care, prescribing pattern and their perceptions, attitudes and experiences regarding the EMPOWER-PAR intervention. This study will also provide a cost-effectiveness analysis of conducting a multifaceted intervention using readily available resources in a resource-constrained setting.

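### The cost-effectiveness ratio is conditional on significant differences in both cost and effect, so inconclusive results get no ratio and any reported ratio carries selection bias of unknown direction

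*Protocol article*

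**What the plan says.** The Cost-effectiveness analysis section sets the rule: "If the intervention group was statistically more expensive and effective than usual care group, then the incremental cost effectiveness ratio was calculated". It defines the ratio as "the difference between the costs for each group divided by the difference in effectiveness" and adds: "The threshold of MYR 31,195 was used to determine the cost-effectiveness of the intervention". It states no rule for the other possible results: more effective with an inconclusive cost difference, costlier with an inconclusive effect, or cheaper.

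Elsewhere the commitment has no condition. The Secondary outcomes section lists cost-effectiveness of the intervention as an outcome in its own right. The abstract says that the results "will provide objective evidence of the effectiveness and cost-effectiveness of a multifaceted intervention", and the Discussion says: "This study will also provide a cost-effectiveness analysis of conducting a multifaceted intervention using readily available resources in a resource-constrained setting".

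The sample size sections cover only the HbA1c and blood pressure proportions. For diabetes the design has 10 clinics "with 63 subjects from each cluster to achieve 91% power to detect 25% difference in the proportion of subjects" reaching the HbA1c target. The article gives no cost difference, no standard deviation of cost and no power for cost.

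**The concern.** Whether an intervention is worth its cost at a given threshold is one question about two quantities taken together. Two separate significance tests do not answer it. A clear gain in control with a modest, imprecisely estimated extra cost could be good evidence of value, yet the rule gives it no ratio.

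The rule also selects. Estimates that have passed a significance test are on average too large. Requiring a significant effect inflates the denominator and pulls the ratio down. Requiring a significant extra cost inflates the numerator and pushes the ratio up.

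At stake is the promised policy evidence. The ratio may be absent when it is wanted, and may be distorted by an unknown amount when it is present.

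**Working it through.** **The plan's own figure.** Effectiveness power, two-sided unpooled Z-test with a design effect:

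power = Φ( d / SE − 1.96 ), SE = √{ [p₁(1−p₁) + p₂(1−p₂)] × [1 + (m−1)ICC] / n }

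From the article for diabetes: d = 0.25, m = 63, n = 313 per arm, alpha 0.05. The article gives neither the intracluster correlation (ICC) nor the control proportion. I assume ICC 0.05 and 50% rising to 75%.

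- Diabetes: design effect 1 + 62 × 0.05 = 4.1. SE = √(0.4375 × 4.1 / 313) = 0.0757. Signal 0.25 / 0.0757 = 3.30. Power Φ(1.34) = 91%, as stated.
- Hypertension (m = 44, n = 219): design effect 3.15, SE = 0.0793, signal 3.15, power 88%, as stated.

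The design effect on HbA1c is therefore a signal (true difference divided by its standard error) of about 3.3.

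**How often the ratio would be reported.** I assume that the estimated cost and effect differences are independent and that each must exceed 1.96 standard errors. Then P(reported) = power on effect × power on cost. At the design effect:

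| Power on cost (assumed) | Calculation | Ratio reported |
|---|---|---|
| 17% | 0.91 × 0.17 | 15% |
| 50% | 0.91 × 0.50 | 46% |
| 80% | 0.91 × 0.80 | 73% |
| 91% | 0.91 × 0.91 | 83% |
| near 100% | 0.91 × 1 | 91% |

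The ratio is missing more often than not only if power on cost is below 0.50 / 0.91 = 55%.

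A smaller effect can be illustrated with the 12 points (57.6% to 69.6%) seen in the earlier Malaysian private-clinic study cited in the Background. With ICC 0.05:

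- Diabetes, 18.1% to 30.1%: 0.12 / 0.0685 = 1.75, power Φ(−0.21) = 42%.
- Hypertension, 57.6% to 69.6%: 0.12 / 0.0810 = 1.48, power Φ(−0.48) = 32%.

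Even a certain significant extra cost would then leave the ratio missing in 58% to 68% of trials.

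These figures use normal critical values. A t reference with 8 degrees of freedom (10 clinics) would lower them; at signal 3.3 the effectiveness power becomes 82%.

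**Direction of the selection bias.** For a true signal μ, the mean exaggeration of an estimate that passes is

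k(μ) = { μ + φ(1.96−μ) / [1 − Φ(1.96−μ)] } / μ

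This gives k(1) = 2.49, k(1.39) = 1.86, k(1.96) = 1.41, k(3.3) = 1.05, and k = 1.00 for a near-certain difference. The bias in the ratio is roughly k(cost) / k(effect). Simulation of the double condition, with independent differences, gives these medians:

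| Effect signal | Cost signal | k(cost) / k(effect) | Median reported / true ratio |
|---|---|---|---|
| 3.3 | 1 | 2.49 / 1.05 = 2.37 | 2.37 |
| 3.3 | 1.96 | 1.41 / 1.05 = 1.34 | 1.33 |
| 3.3 | 3.3 | 1.00 | 1.00 |
| 3.3 | 10 | 1.00 / 1.05 = 0.95 | 0.96 |
| 1.96 | 10 | 1.00 / 1.41 = 0.71 | 0.74 |
| 1.39 | 1.96 | 1.41 / 1.86 = 0.76 | 0.75 |
| 1.39 | near certain | 1.00 / 1.86 = 0.54 | about 0.55 |

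A value above 1 makes the intervention look worse value than it is, and a value below 1 makes it look better. The less certain of the two differences sets the direction.

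**The case against.** - **Only the ratio is conditional.** The section computes average total cost per patient for each arm, and the Statistical analysis section estimates treatment effects with no significance condition. Nothing says that either is withheld, and a cheaper, more effective intervention needs no ratio. This stands. The defect is narrower than a missing economic analysis.
- **The text says if, not only if.** That is so, but no other case is given, so the restrictive reading is fair.
- **Detail on uncertainty belongs in a fuller plan.** This also stands: the article's silence on intervals is not the point here. The significance condition is different, because the article states it.
- **A reader might infer that the ratio will usually be suppressed.** The documents do not support this. It depends on power for cost and on the true effect, neither of which is given. Workshops, booklets and facilitation are charged to the intervention, so a clearly significant extra cost is plausible; the ratio would then be reported in most trials at the design effect.
- **A reader might also infer that a reported ratio is biased in the intervention's favour.** That holds only when the effect is the less certain quantity. At the design effect with 50% power on cost, the median is 1.33 times the truth, which is against the intervention. Understatement by nearly half needs both a weak effect and a near-certain extra cost.

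**Conclusion.** The point holds in this limited form. A stated rule makes the ratio depend on two significance results, while the same article lists and promises cost-effectiveness without condition. Inconclusive results are left with no ratio to set against the threshold, and a reported ratio carries selection bias whose direction cannot be known in advance.

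The sizes are scenarios, not estimates for this trial. They assume independent, normally distributed differences and rest on unstated values for power on cost, ICC and control proportions. Cost-effectiveness is a secondary outcome and the primary analyses are unaffected. The change should be made, because this is the evidence on value that the article offers to policy makers.

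**What to change.** Delete the significance condition. Report incremental cost and incremental effect, and the ratio or the dominance quadrant, whatever the P-values. Give their joint uncertainty by a method that respects clustering by clinic, for example incremental net benefit at the stated threshold with a cluster-based interval.

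The cost is analysis work only. According to the Trial status section, outcome data had been collected and data cleaning and analysis had only just begun, so no new data are needed.
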